#### Blinding

Patients, doctors and researchers will not be blinded for the treatment allocation. The nature of our study does not allow for blinding of the aforementioned parties. Unblinding does therefore not apply.

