### Outcomes

#### Primary outcome

The difference in change (Δ, preoperatively and postoperatively) in BCTQ score between both treatment groups at 3, 6 and 12 and 18 months follow-up.

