### Statistical methods

#### Primary study parameter

Difference in change in BCTQ: Linear generalized estimating equation (GEE) analyses will be used to study the longitudinal relationship between treatment group (determinant) on the one hand, and BCTQ score (outcome variable) on the other hand. This will be performed for the different domains of the BCTQ. This results in a single regression coefficient representing the population average difference in the outcome variable over time that incorporates between-subject and within-subject correlations.

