#### Analysis plan

Descriptive statistics will be provided using mean with standard deviation (SD), median with interquartile range (IQR) or frequencies/percentages depending on the type of distribution of the data. Distribution of data will be assessed using histograms and skewing.

Values of *p* < 0.05 will considered statistically significant. All analysis will be on an intention- to-treat basis. We will correct for multiple testing, *P*-values will be corrected by the Bonferroni method [21].

For exclusion and dropout, numbers and reasons are reported to ensure internal validity. A flow- chart will show the number of patients lost during follow-up including reasons for the loss of follow-up. An analysis on basic characteristics will be performed to control for selection bias. Missing values will be imputed using multiple imputations when meeting the assumption of missing completely at random/missing at random (MCAR/MAR), as imputation will always increase precision and often also reduce bias [22, 23].

Table 1 shows the variables at each study visit.

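### Imputation depends on a missing-data assumption that the data cannot confirm, and withholding it leaves only unimputed GEE, which in general assumes more

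*Protocol article*

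**What the plan says.** All references are to the protocol article.

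- **Analysis plan**, the imputation rule: "Missing values will be imputed using multiple imputations when meeting the assumption of missing completely at random/missing at random (MCAR/MAR"). The reason given is "as imputation will always increase precision and often also reduce bias". The section gives no criterion for judging the assumption and does not say what is done if it is judged not to hold. It also promises numbers and reasons for dropout, a flow chart, and an analysis of basic characteristics to address selection bias. On the analysis principle it says: "All analysis will be on an intention- to-treat basis".
- **Primary study parameter**, the primary analysis: "Linear generalized estimating equation (GEE) analyses will be used to study the longitudinal relationship between treatment group" and the BCTQ score. No weighting for dropout and no working correlation is named. On the estimate: "This results in a single regression coefficient representing the population average difference in the outcome variable over time".
- **Primary outcome**: the difference in change "in BCTQ score between both treatment groups at 3, 6 and 12 and 18 months follow-up".
- **Blinding**: "Patients, doctors and researchers will not be blinded for the treatment allocation".
- **Sample size, recruitment and consent**: 10% dropout is allowed for, taking 144 patients to 160. The MCICs listed for the two BCTQ scales run from 0.3 to 0.7 points, and the SD is 0.7.

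**The concern.** The sentence on imputation is a decision rule, and it has two faults as written.

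First, it cannot be operated objectively. MAR and not-at-random missingness differ only in how dropout relates to values nobody has seen. Comparing the basic characteristics of leavers and stayers can give evidence against missing completely at random (MCAR). It cannot show that MAR holds. Whether to impute therefore becomes a judgement made after the data are in, by people who know the allocation.

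Second, it points the wrong way. Multiple imputation is valid under MAR. If MAR is doubted and imputation is withheld, the only primary analysis the article names is GEE on the observed rows, which in general needs a stronger assumption.

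This matters because the trial is open, the primary outcome is self-reported, and follow-up lasts 18 months. Patients unhappy with one technique may stop returning questionnaires. The observed rows would then flatter that arm, which is unwelcome in a trial described as non-inferiority.

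**Working it through.** **1. The plan's own figure.** 144 / (1 − 0.10) = 160, so the dropout allowance reproduces. It covers lost numbers only and says nothing about bias.

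**2. The rule, case by case.**

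| Team's judgement | What the article then provides | Missingness assumption needed |
|---|---|---|
| MCAR or MAR accepted | Multiple imputation, then GEE | MAR |
| MAR doubted | Nothing stated; only the GEE on observed rows remains | In general MCAR, or dependence only on modelled covariates |

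The second row is an inference from the two sections read together.

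**3. Bias at one visit.** Let f be the fraction missing in one arm and g the gap by which its leavers are worse than its stayers. The full-arm mean is (1 − f) × stayers + f × (stayers + g), so the stayers' mean differs from it by f × g. If the other arm's leavers are typical, this is the bias in the arm difference. Here f = 0.10 comes from the article. The values g = 0.5 and 1.0 are assumptions.

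- g = 0.5: 0.10 × 0.5 = 0.05 points. That is 0.05 / 0.3 = 17% of the smallest listed MCIC and 0.05 / 0.7 = 7% of the largest.
- g = 1.0: 0.10 × 1.0 = 0.10 points, or 33% and 14%.

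**4. Bias on the single over-time coefficient.** Suppose (an assumption) that loss builds evenly to 2.5, 5, 7.5 and 10% at the four visits. The average is 25 / 4 = 6.25%.

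- g = 0.5: 0.0625 × 0.5 = 0.03 points.
- g = 1.0: 0.0625 × 1.0 = 0.06 points.

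If instead all loss came before 3 months, every visit would have 10% missing and the coefficient would carry the full 0.05 to 0.10.

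**5. How far the working correlation matters.** A large-sample simulation used inputs that are not in the article: no true effect, four visits, SD 0.7, exchangeable correlation 0.7, and MAR dropout driven by the last observed score in opposite directions in the two arms. Bias of the unimputed GEE coefficient, in points:

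| Final dropout | Independence | Wrong AR(1) | Correct correlation |
|---|---|---|---|
| 9.5% to 13.0% | 0.04 to 0.07 | 0.01 to 0.02 | about 0 |
| 19.1% to 23.8% | 0.06 to 0.12 | 0.01 to 0.02 | about 0 |
| 30.2% to 34.5% | 0.10 to 0.17 | 0.02 to 0.03 | about 0 |

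Simulation error is about 0.003. Unimputed GEE can therefore be biased under MAR, but how much depends on a choice the article does not state.

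**6. The precision claim.** Imputing an outcome only from variables already in the analysis model adds no information, and a finite number of imputations adds Monte Carlo variance. A gain needs informative auxiliary variables, such as PRUNE scores. The word *always* is therefore wrong.

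**The case against.** **The fallback is not written.** A reader might infer that the plan prescribes unimputed GEE when MAR is doubted. It does not; the article is silent, and a fuller analysis plan may fill the gap. This stands as a limit on wording. It does not rescue the conditional rule, which is stated and cannot be verified.

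**GEE does not strictly require MCAR.** A reader might infer that unimputed GEE is invalid under anything weaker. That is too strong: with a correct working correlation the simulated bias was about zero, and with a wrong AR(1) it was small. The article says its coefficient takes within-subject correlation into account, so independence is the least natural reading. This stands, but the article fixes no structure on which to rely.

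**Imputation may not help where MAR fails.** A MAR-based method removes the bias only as far as earlier scores explain the dropout. For patients lost before 3 months there is no earlier postoperative score. This stands, and it is why a not-at-random sensitivity analysis belongs in the fix.

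**The size is small.** With 72 per arm and SD 0.7, the single-visit standard error is 0.7 × √(2/72) = 0.12, so 0.05 is less than half of it. This also stands.

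**The condition may mean plausibility.** It can be read as a judgement informed by reasons for loss, which is common practice. Even so, that judgement is made unblinded and after the data are in.

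**The precision clause may be harmless.** The article does not restrict the imputation model, so a gain is possible, and the clause changes no result by itself.

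**Conclusion.** The concern holds in limited form. The article makes imputation depend on an assumption that observed data cannot confirm and leaves that decision to an unblinded team. If imputation is withheld, the only primary analysis it names is one that in general assumes more about the missing data.

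The bias at stake at 10% dropout is modest: 0.05 to 0.10 points at a fully affected visit, and about 0.03 to 0.06 on the over-time coefficient if loss builds evenly. These figures rest on an assumed gap of 0.5 to 1.0 points, confined to one arm, and on rows that are simply left out. They are small to moderate against MCICs of 0.3 to 0.7; the article does not say which MCIC drove the sample size. The documents do not support a conclusion that dropout at the planned rate would by itself overturn the trial's result.

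The change is worth making because the rule is faulty as stated and cheap to correct. The precision claim is a wrong rationale only.

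**What to change.** 1. Delete the condition on MCAR/MAR and fix one MAR-based primary analysis for every case. Either impute by arm, using baseline and all observed BCTQ and PRUNE scores, and then fit the GEE; or fit a likelihood-based mixed model to all rows. Choose one before the data are seen.
2. Add one pre-specified not-at-random sensitivity analysis: shift the imputed values by arm over a stated range, for example 0.1 to 0.7 points, and report where the conclusion changes. If the mixed model is chosen, imputed values are still needed for this step.
3. Reword the rationale to say that imputation can increase precision when informative auxiliary variables are used.

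The cost is revised wording and a little more analysis work. No new data, visits or patients are needed.

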## Discussion

As yet, no gold standard for cubital tunnel release exists, both the open and endoscopic approaches are commonly used. The two techniques have been compared, but not in an extensive RCT design with sufficient participants and including PROMs and PREMs.

Moreover, modern medicine increasingly focusses on improving treatment through understanding patient’s perspectives on health quality. PROMs and PREMs seem particularly important in surgical procedures as objectives measures might not adequately reflect success of these treatments. For that reason, PROMs and PREMs are increasingly used in clinical practice. Therefore, including these measurements in trials is an important addition to the current literature.

Randomized controlled trials (RCTs) are considered the most effective way to indicate relationships of cause and effect between interventions and outcomes.

It is expected that with this open randomized trial design including PROMs and PREMs, we will be able to make evidence based recommendations on best efficacy, patient treatment experience and safety profile regarding open and endoscopic cubital tunnel release. Moreover, since cubital tunnel is the second most common entrapment syndrome of the upper extremity, including patient’s experiences could increase quality of care and eventually quality of life on a large scale in the future.

## Data Availability

The dataset generated during this study are available from the corresponding author on reasonable request and will be published in a scientific article.

## Abbreviations

BCTQ: Boston Carpal Tunnel Questionnaire
EMG: Electromyography
EVOCU: Endoscopic versus Open Cubital Tunnel Release
GEE: Generalized Estimating Equation
IQR: Interquartile Range
MAR: Missing At Random
MCAR: Missing Completely At Random
MCIC: Minimal Clinically Important Change
METC: Medisch Ethische Toetsings Commissie
MREC: Medical Research Ethics Committee
PC: Phone Call
POSAS: The Patient and Observer Scar Assessment Scale
PREMs: Patient Reported Experience Measures
PROMs: Patient Reported Outcome Measures
PRUNE: Patient Rated Ulnar Nerve Evaluation
RCT: Randomized Controlled Trial
REDcap: Research Electronic Data Capture
RTW: Return To Work
SD: Standard Deviation
VAS: Visual Analog Scale
